### Allocation

Individuals will be eligible for randomization once their baseline questionnaire is completed. Randomization will be carried out in pairs using a table of random permutations conducted by the Program Manager. One member of each pair will be assigned to the Internet-based group and the other to the control group, using sealed envelopes. This strategy ensures equal allocation to the two groups, and that both have similar characteristics regarding measured and unmeasured background variables (i.e., patient characteristics and lifestyle behavior at baseline, medical comorbidities, and situational/contextual factors), which could potentially affect study outcomes. The Program Manager will hold the sequence of assignments and will dispense the code for each new patient upon request by the Research Assistant (RA). If a participant requests to be withdrawn from the study, the Program Manager will assign the code for the next new patient. The Program Manager  will maintain a record of who was randomized to which group to maintain integrity of planned analysis. Due to the nature of the study, the Program Manager will not be blind to the study arms. Randomization will be ongoing until sample size goals are reached: 100 per study arm and in accordance with the CONSORT randomization guidelines as shown in Fig. 2.

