### Sample size

Guided by principles governing the use of focus group data, the sample size will be determined when we reach a point of “saturation”, which is when additional group sessions are not likely to produce new themes. Based on previous research [49, 50], we expect that five groups will be sufficient to capture key themes for the project. In the secondary objective - assuming a medium effect size (d = 0.32), as derived from Cohen [51], and a sample size of 200 - the study will be adequately powered (>85%) to detect significant differences between participants likely to show improvement in health literacy scores and those who are not using Fisher’s exact tests (critical X^2^ = 7.98). In a previous pilot study, we found that 40% of black patients in the community adopted recommendations for OSA treatment after exposure to health messages, which compares to 27% who did without such exposure. Assuming a 13% increase in the likelihood of adoption of health messages and a sample size of 200, the proposed study will have adequate power for a preliminary test of the hypothesis that exposure to health messages will foster improvement in sleep health literacy. Achieving the goal of a 13% increase would have an important public health impact. A two-tailed test, with 85% power and α = 0.05 comparing 27% to 40% requires 100 participants per arm [52].

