Both selection and attrition biases might occur during data acquisition for aim 3. Selection bias might result from participant’s refusal to participate and attrition bias could result in an unbalanced design. Appropriate statistical techniques (e.g., Heckman two-stage approach GEE probit model, and Monte Carlo [53] will be used to address such biases, or problems that might result from missing data. Adequate statistical corrections will be made in final statistical analyses to increase generalizability of the findings. Sociodemographic data obtained from those who did not participate will be used to determine whether they are similar to those in the study [54]. Likewise, baseline characteristics of participants who withdrew from the study will be contrasted with completers to determine whether any attrition bias may have occurred.

The Biostatistician will manage study data under the PI’s supervision. He will create computerized data collection forms to ensure integrity and accuracy of data entry. He will help to minimize the problem of missing data by resolving omissions and errors as they arise. Throughout the study, the PI will oversee data entry and verification, ensure adherence to coding, and clean and edit protocols. Participant-identifying information will be kept in a locked file cabinet with only numerical identifiers in computer files.

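### The stated 85% power at 100 per arm is not available: it is about 50% with complete data, and the sizing leaves no room for the attrition the protocol foresees

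*Protocol article*

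**What the plan says.** The Sample size section of the protocol article gives two justifications for 200 participants.

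- The first rests on a standardised effect, "assuming a medium effect size (d = 0.32), as derived from Cohen", with power above 85% by Fisher's exact test.
- The second rests on pilot proportions. For the exposed group the section reports: "we found that 40% of black patients in the community adopted recommendations for OSA treatment after exposure to health messages". The corresponding pilot rate in the unexposed group was 27%. The section concludes: "A two-tailed test, with 85% power and α = 0.05 comparing 27% to 40% requires 100 participants per arm".

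The Allocation section sets the stopping point for enrolment: "Randomization will be ongoing until sample size goals are reached: 100 per study arm". It adds that when a participant asks to be withdrawn, the Program Manager assigns the code for the next new patient.

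The Statistical analysis section says: "Both selection and attrition biases might occur during data acquisition for aim 3". It names techniques for such biases and for missing data, and plans to compare the baseline characteristics of withdrawals and completers. It gives no expected rate of loss. The comparison of participants who improved with those who did not is placed at 2 months.

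**The concern.** The number said to be required for the test and the number to be randomised are both 100 per arm. Since both are printed and equal, no allowance for missing outcomes can lie between them. The outcome is a questionnaire score at 2 months, and some missed questionnaires are likely enough that the authors plan for them.

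That prompts a check of what power the design has at 100 per arm and at somewhat fewer. If the printed 85% is too high, readers and funders will give a null result on hypothesis 3 more weight than it deserves. Missing-data methods can reduce bias from loss, but they do not recreate the information that was lost.

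**Working it through.** **Inputs from the protocol article.** Two-sided α = 0.05, power 85%, proportions 0.27 and 0.40, d = 0.32 (all Sample size); 1:1 allocation with 100 per arm (Allocation). No loss rate is given, so 5 to 20% at 2 months is my assumption.

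**Step 1: reproduce the stated 100 per arm.** Pooled-variance normal approximation, with p̄ = (0.27 + 0.40)/2 = 0.335:

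n = [z₀.₉₇₅·√(2p̄(1−p̄)) + z₀.₈₅·√(p₁(1−p₁) + p₂(1−p₂))]² / (p₂−p₁)²

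- √(2 × 0.335 × 0.665) = 0.6675
- √(0.27 × 0.73 + 0.40 × 0.60) = 0.6611
- n = [(1.960 × 0.6675 + 1.036 × 0.6611)/0.13]² = 235.1, so **236 per arm**

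The stated 100 does not reproduce. Variants at 85% power:

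| Variant | n per arm |
|---|---|
| Continuity correction | 251 |
| Unpooled variance | 233 |
| Arcsine | 235 |
| One-sided | 189 |

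Dropping to 80% power, two-sided, gives 206. Even a one-sample test against a fixed 27% gives 91 (one-sided) or 113 (two-sided).

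**Step 2: power at 100 per arm with complete data.**

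Power = Φ{[0.13·√n − 1.960 × 0.6675]/0.6611}

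At n = 100 this is Φ[(1.300 − 1.308)/0.6611] = Φ(−0.013) = **49.5%**. Fisher's exact test, which the section names for its d = 0.32 calculation, gives 43.5% by enumeration.

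**Step 3: the other input, d = 0.32 as a standardised mean difference.** The noncentrality is d·√(n/2) = 0.32 × √50 = 2.263. The two-sided t test then has power **61.5%** (61.9% by normal approximation). For 85% the normal approximation needs 2 × [(1.960 + 1.036)/0.32]² = 175.4, so 176 per arm.

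**Step 4: the effect of assumed loss.** The formulas of steps 2 and 3, with fewer evaluable per arm:

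| Assumed loss | Evaluable per arm | Power, 27% vs 40% | Power, d = 0.32 (t test) |
|---|---|---|---|
| 0% | 100 | 49.5% | 61.5% |
| 5% | 95 | 47.5% | 59.3% |
| 10% | 90 | 45.5% | 57.0% |
| 15% | 85 | 43.4% | 54.6% |
| 20% | 80 | 41.3% | 52.1% |

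Fisher's exact test at 80 per arm and 27% vs 40% gives 35.6%.

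**Step 5: split the shortfall (27% vs 40%).** Base calculation: 85 − 49.5 = 35.5 points. Attrition at 10 to 20%: 49.5 − 45.5 = 4.0 to 49.5 − 41.3 = 8.2 points.

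**Step 6: what the design can detect.** Solving the step 2 formula for p₂, with p₁ = 0.27, power 85%, and the two square roots recomputed for each p₂, gives 47.3% at 100 per arm, 48.5% at 90 and 49.8% at 80. The detectable difference is thus about 20 to 23 percentage points, not 13.

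**The case against.** **The protocol does not forecast attrition.** This stands. The wording is conditional throughout, and naming a risk with a contingency analysis is not an expected rate. A reader might infer that the sample-size and analysis sections contradict each other. The text does not support that: it shows a power figure that needs complete data beside an acknowledged possibility that data will be incomplete.

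**Attrition is not the main cause.** This also stands. A reader might infer that 100 per arm is a sound 85% calculation spoiled only by dropout. Step 2 rules that out, because power is about 50% with nobody lost. Adding a dropout allowance to 100 per arm would only preserve that 50%.

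**Withdrawals may be replaced.** The Allocation sentence on withdrawal can be read that way, so zero replacement cannot be assumed. Even on the generous reading it covers only people who ask to leave while enrolment is open. Missed 2-month questionnaires and losses after the last assignment remain uncovered.

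**This is a condensed article.** An expected dropout rate may sit in a fuller protocol, and its absence here is not the finding. The finding is a printed power that its own printed inputs do not yield.

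**d = 0.32 might be meant as Cohen's w.** Read so, N = 200 gives about 99% power at 1 degree of freedom. But 27% versus 40% corresponds to w = 0.13/(2·√(0.335 × 0.665)) = 0.14, so this reading does not support the proportion-based claim. The article also writes d.

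**The test is called preliminary.** That is a fair description of the aim, but it does not make the stated 85% correct.

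**Conclusion.** The concern holds with attrition in second place. For the protocol's own 27% versus 40% at two-sided 0.05, 100 per arm gives about 50% power with complete data, against a stated 85%; about 236 evaluable per arm would be needed. Reading d = 0.32 as a standardised mean difference gives about 61%.

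Because randomisation stops at the number said to be required, any loss lowers power further: to about 46 to 41% for the proportions, and 57 to 52% for d = 0.32, at 10 to 20% loss. The complete-data figures rest only on printed inputs. The loss range is assumed, and it treats loss as equal in both arms and without replacement. Replacement of withdrawals would shrink the second effect but leave the first untouched.

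**What to change.** In the Sample size section, keep 200 randomised and:

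1. Say that 100 per arm is the number randomised, not the number with outcome data.
2. State an assumed loss at the 2-month outcome and its basis.
3. Replace the 85% claim with the recomputed power for 27% versus 40%, or with the detectable difference, at the resulting evaluable number (for example 80 to 90 per arm: about 41 to 46% power, or 85% power for 27% versus about 49 to 50%).
4. Treat the d = 0.32 statement the same way, and say what the effect size measures.

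In the Allocation section, clarify whether the withdrawal sentence means that a withdrawn participant is replaced, and until when.

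This takes a few sentences and no extra participants. The price is a less favourable stated power. Simply inflating 100 per arm for dropout would not restore 85%. Keeping 85% for a 13-point difference would need about 236 evaluable per arm, or 236/0.90 = 263 to 236/0.80 = 295 randomised per arm at 10 to 20% loss.

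### The stated 100 per arm for 27% versus 40% at 85% power is wrong: those inputs need 236 per arm, and 100 per arm gives about 50% power.

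*Protocol article*

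**What the plan says.** All inputs are in the Sample size section of the protocol article. The rates come from the investigators' pilot study. For the exposed group it reports: "we found that 40% of black patients in the community adopted recommendations for OSA treatment after exposure to health messages". The pilot rate in patients not exposed was 27%. The section then claims adequate power for a preliminary test: "Assuming a 13% increase in the likelihood of adoption of health messages and a sample size of 200". It closes with the calculation itself: "A two-tailed test, with 85% power and α = 0.05 comparing 27% to 40% requires 100 participants per arm".

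The Allocation section turns this number into the recruitment target: "Randomization will be ongoing until sample size goals are reached: 100 per study arm".

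Earlier in the Sample size section there is a second, separate power statement. It gives power above 85% with 200 participants for an effect of d = 0.32, called medium and attributed to Cohen, "using Fisher’s exact tests" and quoting a critical chi-squared value of 7.98. The Statistical analysis section makes the main dependent measure for aim 3 a yes/no variable and lists chi-squared tests among the planned comparisons.

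**The concern.** A 13-point difference between proportions near one third usually needs well over 200 per arm for 85% power, so 100 looks too small by more than half.

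The section says that a 13% increase would matter for public health, and recruitment stops at 100 per arm. If the true power for that difference is about one half, the trial would miss a benefit of the planned size about as often as it found it. A non-significant result would then be read as evidence against tailoring, on the strength of a stated 85% power that the trial does not have.

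**Working it through.** **Inputs, all from the Sample size section:** control rate p1 = 0.27, exposed rate p2 = 0.40, difference 0.13, two-sided alpha 0.05 (z = 1.960), power 85% (z = 1.036). Equal allocation with 100 per arm also stands under Allocation. The mean rate is (0.27 + 0.40)/2 = 0.335.

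**1. Attempt to reproduce 100 per arm.** Pooled-variance formula:

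n = [1.960 × √(2 × 0.335 × 0.665) + 1.036 × √(0.27 × 0.73 + 0.40 × 0.60)]² / 0.13²

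= [1.960 × 0.6675 + 1.036 × 0.6611]² / 0.0169 = [1.3083 + 0.6852]² / 0.0169 = 235.1, so **236 per arm** (472 in total).

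Variants, per arm:

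| Method | n per arm |
|---|---|
| Pooled, two-sided, 85% | 236 |
| Unpooled, two-sided, 85% | 233 |
| Arcsine, two-sided, 85% | 235 |
| Continuity-corrected, two-sided, 85% | 251 |
| Fisher's exact test, full enumeration | about 250 (power 84.9% at 248, 85.2% at 250) |
| Pooled, two-sided, 80% | 206 |
| Pooled, one-sided, 85% | 189 |
| Pooled, one-sided, 80% | 162 |

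None of these gives 100.

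**2. Power at 100 per arm for 27% versus 40%.** Normal approximation:

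z = [0.13 × √100 − 1.3083] / 0.6611 = (1.3000 − 1.3083) / 0.6611 = −0.0125, so power is 49.5%.

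Full enumeration of the two binomial distributions gives 49.8% for the uncorrected chi-squared test and 43.5% for Fisher's exact test. A one-sided test would give 62.0%. Reading 200 as the number per arm, which the Allocation section rules out, gives 78.9% (pooled formula) or 75.9% (Fisher).

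**3. Difference detectable with 85% power at 100 per arm, control rate 27%.** The pooled formula solves at 47.3%. Enumeration gives:
- chi-squared: 85.7% power at 47.5%, a difference of 20.5 points;
- Fisher: 83.8% at 48%, 85.5% at 48.5% and 87.1% at 49%, so about 48.5%, a difference of 21.5 points.

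**4. Whether the d = 0.32 statement supports the figure.**
- As a standardised mean difference with 100 per arm: 0.32 × √(100/2) = 2.263, and 2.263 − 1.960 = 0.303, so power is about 62% (61% with the t distribution). For 85% power, n = 2 × (1.960 + 1.036)² / 0.32² = 175.4, so 176 per arm.
- As Cohen's w with 200 in total, power exceeds 95% for 1 to 5 degrees of freedom. But 27% versus 40% corresponds to w = 0.13 / (2 × √(0.335 × 0.665)) = 0.138, less than half of 0.32.

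On the first reading the claimed power is not met. On the second it is met, but for a much larger effect than the 13-point target.

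**The case against.** The strongest reply is that the section gives more than one basis for its power. A reader might infer from the faulty sentence that the trial has no valid power statement at all. The document does not support that: read as Cohen's w, the d = 0.32 claim is arithmetically true at alpha 0.05. It is still not a defence of the quoted sentence, which fixes its own inputs.

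A reader might also take Fisher's exact test as the test for 27% versus 40% and lead with 250 per arm and 43% power. Fisher is named only in the d = 0.32 sentence. The 27% versus 40% sentence says only that the test is two-tailed, and the Statistical analysis section lists chi-squared tests. So 236 per arm and about 50% are the main figures, and the Fisher results show sensitivity to the test.

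A third tempting addition is that the absence of a dropout allowance is an error. It is not one here. The article condenses a fuller protocol to which it refers, and its Statistical analysis section discusses attrition.

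Finally, effectiveness is the secondary objective, and the section calls this a preliminary test. That tempers the consequence. It does not make an explicit 85% figure correct.

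**Conclusion.** The sentence is wrong as written. Its inputs require 236 per arm by chi-squared, about 2.4 times the stated 100 (236/100 = 2.36), or about 250 by Fisher. The planned trial has about 50% (chi-squared) or 43% (Fisher) power for the 13-point difference, and 85% power only for a difference of 20 to 22 points.

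This rests on independent binary outcomes in two equal arms, on the stated rates, and on all 100 participants per arm contributing. Loss would lower power further. As an illustration only, an assumed 10% to 20% loss (90 to 80 per arm) gives 46% to 42% by chi-squared and 40% to 36% by Fisher.

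**What to change.** In the Sample size section:

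1. Keep 200 participants. Delete the statement that the comparison requires 100 per arm at 85% power, and the claim of adequate power for a 13% increase.
2. State instead that 100 per arm gives about 50% power for 27% versus 40% with a two-sided chi-squared test at 0.05, and 85% power for about 27% versus 47.5%. Give the Fisher figures (43%, and about 27% versus 48.5%) as sensitivity values.
3. Say which effect-size metric d = 0.32 is. Then either restate its power (about 61% to 62% as a standardised mean difference at 100 per arm) or say that, as Cohen's w, it does not correspond to the 13-point target.
4. Report the binary comparison with a 95% confidence interval, so that a null result is not read as coming from an 85%-powered trial.

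Power at the expected number of completers is a useful optional addition. Enlarging the trial or justifying a larger target difference would also make the numbers consistent, but neither is needed to correct the statement. The cost is wording only, and the stated power becomes less favourable.

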### Statistical analysis

Zemke and Kramlinger’s procedures will be used to analyze qualitative data for aims 1 and 2. Focus groups will be recorded and transcribed verbatim. Transcripts will be reviewed line by line and assigned codes or labels to develop themes. Transcripts will be coded and reviewed by two independently trained RAs and the study team will review transcripts in case of any disagreement with codes and themes. For the qualitative data our first hypothesis is that modifiable barriers (e.g., negative beliefs and attitudes toward sleep, perceived bias in healthcare, inadequate access, and lack of cultural and linguistic tailoring of sleep health messages to minorities) will be consistent themes in focus groups. For hypothesis 2: participant engagement will increase acceptability of health messages depicted in posters and dispensed through the interactive website. Stakeholder engagement will facilitate adoption, dissemination, and sustainability of the program. Provider engagement will enable tailoring of health messages addressing participant’s concerns about effectiveness and benefits of different treatment options to inform decision-making. Since we plan to analyze both qualitative and quantitative data, we’ll adhere to Office of Behavioral and Social Sciences Research (OBSSR)-recommended ‘Best Practices for Mixed Methods Research in the Health Sciences’.

For aim 3, we will examine which subjective measures are associated with increased OSA health literacy using multivariate logistic regressions. The main dependent measure will be a binary factor: [yes versus no]; candidate predictors are indicated in Table 1. We will use multivariate analysis to explore whether sociodemographic variables (e.g., age, income, education), lifestyle practices (e.g., diet, exercise, smoking, and drinking habits), Internet self-efficacy, and baseline sleep measures (e.g., OSA knowledge, OSA beliefs, and knowledge of sleep hygiene) indexing OSA health literacy improved after exposure to health messages. We assess OSA health literacy with the Sleep Apnea Literacy scale, a 24 -item questionnaire developed by a sleep expert, and expert in scale design. The questionnaire assesses sleep apnea knowledge and sleep apnea clinical management. Sample items include “When breathing stops during sleep this is called sleep apnea” and “Loud snoring can be a sign of sleep apnea.” Ninety-one participants average age 38, and 48% white, 27% African American completed the questionnaire. The questionnaire was developed using exploratory and confirmatory analyses. The questionnaire includes items across three scales, including sleep apnea literacy (component alpha 0.74), sleep apnea self-efficacy (component alpha 0.76), and sleep apnea clinical management (component alpha 0.65). The concurrent scale validity is 0.85. To compare participants who exhibited improvement in health literacy and those who did not 2 months post-enrollment, *t* tests and chi-squared tests will be used. Multivariate analysis of covariance will be used to assess effects of sleep health messages on sleep measures (e.g., OSA knowledge, OSA beliefs, knowledge of sleep hygiene, and S-TOFHLA scores); effects of confounders will be adjusted. Baseline subjective factors will be entered in a linear regression model in order to determine which factors are associated with higher health literacy scores. In post hoc analyses, we will also explore whether combined effects of exposure to tailored web-based content, and video vignettes received through the website had greater impact on improvement in sleep apnea literacy scores.

Both selection and attrition biases might occur during data acquisition for aim 3. Selection bias might result from participant’s refusal to participate and attrition bias could result in an unbalanced design. Appropriate statistical techniques (e.g., Heckman two-stage approach GEE probit model, and Monte Carlo [53] will be used to address such biases, or problems that might result from missing data. Adequate statistical corrections will be made in final statistical analyses to increase generalizability of the findings. Sociodemographic data obtained from those who did not participate will be used to determine whether they are similar to those in the study [54]. Likewise, baseline characteristics of participants who withdrew from the study will be contrasted with completers to determine whether any attrition bias may have occurred.

The Biostatistician will manage study data under the PI’s supervision. He will create computerized data collection forms to ensure integrity and accuracy of data entry. He will help to minimize the problem of missing data by resolving omissions and errors as they arise. Throughout the study, the PI will oversee data entry and verification, ensure adherence to coding, and clean and edit protocols. Participant-identifying information will be kept in a locked file cabinet with only numerical identifiers in computer files.

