#### Internet Self-Efficacy Scale

This scale will measure confidence in the ability to use the Internet. Participants rate their confidence on a Likert-type scale and are asked statements such as, “using the Internet to gather data” and “turning to an online discussion group when help is needed” [48].

A complete list of measures and the data collection schedule is provided in Table 1.

**Table 1 Tab1:** Study measures and schedule to acquire data

	Time point		
Measures	Baseline	2 months	6 months
Demographic and clinical variables	X		
Medical Outcomes Study Short Form 36	X		
Self-Efficacy Scale	X	X	X
Change Assessment Scale	X	X	X
Intrinsic Motivation	X	X	X
Apnea Risk Evaluation System Questionnaire	X		
Sleep Hygiene Index	X	X	X
Apnea Knowledge/Apnea Belief Scale	X	X	X
Sleep Apnea Literacy Scale	X	X	X
Test of Functional Health Literacy in Adults (short version)	X	X	X
Internet Self-Efficacy Scale	X	X	X

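### The improved yes/no model lets the outcome scale's own baseline score in as a predictor, so regression to the mean can make low scorers look like responders when nobody has changed

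*Protocol article*

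**What the plan says.** In the Statistical analysis section, the aim 3 model is introduced with "we will examine which subjective measures are associated with increased OSA health literacy using multivariate logistic regressions". The outcome and predictors follow: "The main dependent measure will be a binary factor: [yes versus no]; candidate predictors are indicated in Table 1". No cut-off for improvement is given.

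The outcome instrument is named in the same paragraph: "We assess OSA health literacy with the Sleep Apnea Literacy scale". Table 1 schedules that scale at baseline, 2 months and 6 months. Read literally, its baseline value is therefore a candidate predictor. Study arm is not among the measures in Table 1.

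The article says what the multivariable analysis is for. It will explore whether sociodemographic, lifestyle, Internet self-efficacy and baseline sleep factors are "indexing OSA health literacy improved after exposure to health messages". A further step is introduced by "To compare participants who exhibited improvement in health literacy and those who did not 2 months post-enrollment", using t tests and chi-squared tests; the variables to be compared are not listed.

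The effect of the messages on the sleep measures is assigned to a separate, covariate-adjusted MANCOVA.

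**The concern.** A score measured with error that is low at baseline partly by chance tends to be higher next time. When improvement is defined by change on that scale, baseline error raises the predictor and lowers the change. The ordinary test of baseline score against improved yes/no takes no association as its null hypothesis. That null is false for any imperfect scale, whether or not anyone's literacy moved.

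The artefact arises equally in both arms. Half the participants are controls, who do not get the tailored website until 6 months. An association pooled over arms therefore cannot separate response to the tailored messages from this artefact, yet the text attaches it to exposure. At stake is a finding that people with low OSA literacy gain most, which could appear with an inert website.

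**Working it through.** The plan gives no figure of its own on this point, so there is none to reproduce.

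**Inputs from the protocol article**
- 200 participants, 100 per arm (Allocation; Sample size).
- Two-sided alpha 0.05 (Sample size).
- Component alphas 0.74, 0.76 and 0.65 for the literacy scale (Statistical analysis). These are internal consistencies of subscales, not reliability over time.

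**Assumptions**
- Reliability R over time: 0.65 to 0.95.
- Improved means change above 0, or alternatively above 0.5 SD.
- No true change in anyone and no arm effect.

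**Step 1: size of the artefact.** Let Y1 = T + e1 and Y2 = T + e2, with total variance 1 and error variance 1 − R. The change is D = e2 − e1, with variance 2(1 − R), and cov(Y1, D) = −(1 − R). Hence

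corr(Y1, D) = −(1 − R)/√(2(1 − R)) = −√((1 − R)/2).

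At R = 0.74 this is −√0.13 = −0.361. For normal scores, the share of the lower baseline half that improves (change above 0) is 0.5 + arcsin(0.361)/π = 0.617, so about 62% against 38% in the upper half. In simulation the odds ratio is about 0.53 per SD.

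**Step 2: false-positive rate for baseline literacy.** Simulated trials of 200, logistic regression of improved on Y1, Wald test at 0.05:

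| R | change > 0 | change > 0.5 SD |
|---|---|---|
| 0.65 | about 100% | about 100% |
| 0.74 | about 99% | about 97% |
| 0.85 | about 87% | about 76% |
| 0.90 | about 70% | about 52% |
| 0.95 | about 44% | about 17% to 20% |

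Essentially all rejections are in the direction that low scorers improve.

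**Step 3: a different baseline instrument X.** Assume reliability 0.75 and true-score correlation 0.5 with literacy.
- Tested alone with independent error, X is uncorrelated with D, and the rejection rate is about 5%.
- Entered beside Y1, it is no longer neutral. At R = 0.74, corr(Y1, X) = 0.5 × √(0.75 × 0.74) = 0.373. The partial correlation of X with D given Y1 is (0 + 0.373 × 0.361)/√((1 − 0.139)(1 − 0.130)) = 0.155. Simulated rejection is about 45%, 40% and 28% at R = 0.65, 0.74 and 0.85.
- Tested alone, but with same-day error correlated 0.3 or 0.5 with that of the literacy scale, rejection is about 23% or 52% (R = 0.74).

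**Step 4: does an interaction remove it?** In a linear model of Y2 on Y1, arm and Y1-by-arm, the interaction rejects in about 4% to 5% of trials over R = 0.65 to 0.95. With X and X-by-arm added to Y1 and arm in place of Y1-by-arm, the X-by-arm term rejects in about 5% to 6%. Both are close to nominal.

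**The case against.** The strongest reply is that the predictors named in the text are other things: age, income, education, lifestyle, Internet self-efficacy, OSA knowledge, OSA beliefs and sleep hygiene. None is the literacy scale, and each keeps about 5% when tested alone with independent error. This stands, and it limits the point. A reader might infer that every baseline measure will come out as a false predictor; the documents do not support that. But the text also sends the analyst to Table 1, where the literacy scale is listed, and the models are multivariable, so correlated scales can be distorted by standing beside it.

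A second reply is that these analyses are exploratory, that the article states no null hypothesis about differential response, and that a condensed article may leave an arm term to a fuller plan. The missing interaction alone would not be a finding. What can be criticised is on the page: the outcome instrument's own baseline is a candidate predictor, and the result is framed as improvement after exposure.

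A third reply is that the size is uncertain. This also stands. The cut-off is unstated, the alphas are not test-retest reliabilities, and the rate falls well below certainty for a very reliable scale or a strict cut-off. Nor do the documents give any correlation between the scales' errors, so the 23% and 52% figures are illustrations only.

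**Conclusion.** The point holds for the baseline Sleep Apnea Literacy score, and for correlated covariates entered beside it, in the improved yes/no model. It rests on improvement being defined as change from baseline. With no change in anyone, baseline literacy is falsely significant in about 99% of trials at reliability 0.74, and in about 44% to 100% over reliability 0.95 to 0.65 with any rise counted. With a cut-off of 0.5 SD and reliability 0.95, it is about 20% or slightly less.

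Three stronger readings are not supported:
- That the trial is bound to report a benefit in low scorers. The rate depends on two unstated quantities.
- That the improver versus non-improver t tests are necessarily faulty. They share the fault only if baseline literacy is among the variables compared, and those variables are not listed.
- That the randomised comparison is invalid. Message effects are assessed separately by MANCOVA, which this artefact does not affect.

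**What to change.** State that neither the baseline Sleep Apnea Literacy score, nor any covariate entered beside it in the improved yes/no model, will be read as a predictor of benefit. Apply the same rule to the t tests if baseline literacy is compared there.

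For the question of who responds to the messages, model the 2-month Sleep Apnea Literacy score on baseline score, arm, the baseline factor and factor-by-arm. When the factor is baseline literacy itself, the interaction is baseline-by-arm. Interpret only the interaction as differential response: regression to the mean is the same in both randomised arms and cancels there. Describe main effects of baseline factors as prognostic.

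The cost is a change of analysis wording; no new data are needed. The drawback is that interaction tests have low power at 100 per arm, so the analysis should be labelled exploratory.
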